### Procedure

The study will follow a two-step procedure. The first step will be to develop the SG. This will be done by a multidisciplinary team comprising IT engineers and designers who will handle the technical elements of the SG and healthcare professionals who will create realistic content, that is, the clinical vignettes, the distractors, and the visual appearance of each on-screen element. The second step will be to recruit participants in the EDs and deliver the SG.

#### Procedure for constructing the serious game and clinical vignettes

First, a pre-design session will be held to define the different steps in the construction of the SG called *SGTRI* and to describe the tasks to be performed by the game developers, the clinical partners, and the research team. Second, the design session will cover all the elements required to recreate the ED triage environment, such as the graphic interface, clinical vignettes, adjunctive distractions, and triage tasks. The SGTRI will be designed on and operated from an open-source platform called *Wegas* (http://www.albasim.ch). To develop *SGTRI* and allow it to evolve, the research team will use a logical graphic interface that may include audio-visual elements adaptable to needs and scenarios. This graphic interface will consist of a virtual 2D waiting room that will be the stage for different animated clips where patients may arrive by ambulance or by foot and other healthcare workers (paramedics, doctor) may be present. A triage workstation will be recreated from 2D plans based on the ED triage observations of a designer on the research team. This triage station will be equipped with all the devices used by nurses under the circumstances (e.g., triage form, clock, computer).

The clinical vignettes will be developed in conjunction with an emergency clinical specialist nurse, an emergency medicine professor (the initiator of SETS® development), and a certified emergency nurse. All these experts have numerous years of experience in the emergency field and with the triage process. A series of 20 interactive clinical vignettes will be created based on a retrospective review of real cases in an emergency department. The clinical vignettes will be constructed following the three quality guidelines proposed by Evans et al. [69]: (1) each vignette must simulate situations faced by participants, which will be the case in this study; (2) each vignette must be different and entail a specific decision to be made, which in our case will be to assign an emergency level; and (3) using well-designed vignettes must produce a highly generalizable “real-life” triage process. For each clinical vignette, the emergency level will be validated by mutual agreement by a group of four experts (two staff physicians and two nursing experts), in strict compliance with the criteria and definitions of the SETS® [20]. This will constitute the gold standard. For our study, the clinical vignettes will involve the medico-surgical issues most encountered in ED and all four emergency levels of the SETS will be covered. To create an immersive ED environment, we will select noises and task interruptions based on real-time observations and recordings by members of the research team in different ED triage settings and on a review of the scientific literature, using the instrument developed by Johnson and colleagues [70] for classifying task interruptions during nurse triage.

In each experimental group (A, B, C), 10 interruptions and/or noises will be introduced in different clinical vignettes. The distribution of task interruptions (type, number, and duration) will follow a predetermined sequence generated by the researchers. The SG will leave the nurse participants the choice of responding or not to some task interruptions (e.g., an incoming telephone call) but will require them to respond to others (e.g., a patient inquiring about the wait time). The noise will correspond to the soundscape (observed values) of triage stations. The research team will modulate the noise exposure condition by varying the form, length of exposure, and intensity of the ambient noise (e.g., conversation, telephone ringtone). The intensity of the noise exposure will range from 35 (A) to 85 dB (A), the maximum level at which no auditory protection is required [71]. To immerse nurses in the created soundscape and eliminate extraneous noise, nurses will be required to wear headphones during the SG session.

Lastly, triage nurse activities will be identified and designed to correspond as much as possible to real-life tasks. These will be the most common tasks performed by nurses at triage, such as taking the patient’s clinical history through a list of predetermined questions (e.g., Are you in pain?), measuring vital signs (e.g., blood pressure), recording patient clinical values, and transcribing the emergency level and chief health complaint. Once the *SGTRI* is designed, a pre-test will be planned with eight clinical emergency experts. The aim of the pre-test will be to assess all the processes to correctly implement the SG during the recruitment phase.

#### Procedure for participant recruitment and SG delivery

First, the aims of the research will be presented at the annual meeting of ED SETS® users. Second, all the care facilities with an emergency unit in the five cantons of the French-speaking part of Switzerland (Geneva, Vaud, Fribourg, Jura, Neuchâtel) will be contacted to validate their interest in participating in the study. Third, nurses interested in participating in the study will receive an information and consent form. The definitive list of participants will be drawn up after consent forms are signed. Nurses will be block-randomized across the four groups just before starting the SG by order of arrival for the test. Each participant will then be assigned an identification number when they start the SG. Fourth, the study data will be collected directly in each ED by the research team. During the session, the research team will be on site to ensure nurse participants are correctly assigned and to ensure fidelity of SG session delivery.

SG delivery will comprise four stages. First, participants will receive a 30-min research project information and training session led by a member of the research team. Second, the participants will run through a training session composed of two clinical vignettes that will not be included in the analyses. During this session, the participants will familiarize themselves with the equipment (headphones, laptop) provided by the members of the research team. Third, once the training session is completed, each nurse will be able to start their SG session when ready. The nurses will have 2 h to complete the 20 clinical vignettes. This corresponds to the average number of patients triaged at an ED over 2 h. To establish a controlled set for the SG, participants will be isolated in a meeting room previously prepared by the head nurses in each participating emergency unit. Members of the research team will be on site to provide technical support, if needed, and to document any technical problem that might occur during the SG. Fourth, once the 2 h has elapsed, each participant will stop the game session even if not all 20 vignettes have been evaluated. All the data collected during the SG session will be automatically recorded, and they will be saved on a secured server located in Switzerland. After their 2-h SG session, the participants will return to their workplace.

### Instruments

Sociodemographic data, both personal (gender, age, family situation) and professional (employment status, total number of years of experience, number of years in current department), will be collected through a questionnaire developed on the basis of elements gathered in previous studies of triage accuracy [27, 35, 72].

The clinical decision-making of the nurse participants will be judged on the emergency level that they assign based on the SETS® criteria. Following their clinical reasoning, nurses assign patients an emergency level from 1 to 4. The scale has been the focus of various independent studies [20, 73] where computerized clinical vignettes were used with ED nurses and paramedics.

Nurse level of confidence in their clinical decision-making will be measured using a visual analogue scale from 0 to 100 [74]. This scale will be presented to nurses after each emergency level assignment. The question asked will be: “Now that you have completed this clinical vignette, how confident are you of the emergency level that you have assigned?” Nurses will rate their confidence from 0 to 100, with 0 corresponding to “I am not at all confident of my decision” and 100 to “I am fully confident of my decision.” Visual analogue scales allow measuring the intensity of a subjective experience and are widely used in clinical settings [66]. In a study where the scale was used by 69 nurses in a triage situation, the researchers reported no problems with its utilization [35].

The feasibility of the SG will be assessed on the basis of criteria drawn from Sidani and Braden [44] and Feeley et al. [75], including accessibility of target population, appropriateness of inclusion and exclusion criteria, participation rate, withdrawal rate after starting SG, presence and frequency of problems during delivery of SG (understanding, utilization, clarity), presence and frequency of missing data and outliers, and participant satisfaction with SG.

The acceptability of the SG will be measured using a French version of the self-administered AttrakDiff 2 inventory [76] initially developed in German by Hassenzahl and colleagues [77]. This 28-item scale allows evaluating the hedonic and pragmatic qualities of interactive systems such as SG. Each item takes the form of a 7-point scale (− 3 to + 3) on which to rate a quality expressed by semantic differentials, that is, a pair of antonyms. It comprises four subscales: usability, functionality, social impact, and attractiveness. For each item, the respondent must choose between seven answers book-ended by the semantic differentials. A mean score and standard deviation are calculated for each dimension, taking account of certain inverted items [76]. The values between 0 and 1 are considered neutral. Dimensions are deemed positive if scored between + 1 and + 3 and negative if scored between 0 and − 3, in which case the SG needs to be improved. The psychometric properties (validity and reliability) of the French-language scale are entirely satisfactory, having obtained a Cronbach’s α of 0.75 for each of the dimensions [78]. A supplementary question in the form of a visual analogue scale from 0 to 100 will be added to examine how realistic the nurses perceive the SG to be relative to their professional activity.

### Data analysis plan

The nurse participants (expected *N* = 80) will be the analysis units for the descriptive analyses, and the assigned triage scale scores will be the analysis units for the correlational analyses and some descriptive analyses (number of nurses multiplied by number of vignettes—expected *N*: 80 × 20 = 1600). The following data analysis plan will be carried out to answer the research questions: First, the collected data will be verified (compliance with inclusion criteria, identification of missing data and outliers). Second, the data on the nurses (sociodemographic and professional) will be analyzed via descriptive statistics, both univariate (mean, median, standard deviation, interquartile range, and absolute and relative frequency) and bivariate (contingency table and marginal frequency). Third, triage accuracy will be measured by the level of agreement between the answers given by the nurses and the gold standard established by the experts. For each nurse, the scores assigned to each clinical vignette will be compared against the gold standard. The results of the comparison will be a three-level multinomial variable: accurate triage (nurse score same as gold standard), overtriage (score higher than gold standard), and undertriage (score lower than gold standard). Over- and undertriage frequencies will be used to describe the triage accuracy of the four groups, that is, the control group and the three experimental groups: noise (A), task interruptions (B), and noise and task interruptions (C). Fourth, to examine the individual and combined effects of the distractors on the triage accuracy of the nurse participants, the groups will be compared against one another using a random-intercept multinomial regression model. For all the analyses, the statistical significance level will be *p* ≤ 0.05. All the data will be analyzed using the R statistical software [79].

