### Theoretical framework

The theoretical framework chosen for the study is an adapted version of the Systems Engineering Initiative for Patient Safety (SEIPS) model [45]. It is a framework frequently used in human factors analysis and patient safety research to gain insight on performance in different healthcare settings, including emergency departments [46–48]. The model comprises three dimensions: work system, processes, and outcomes. It has three main strengths. First, it can describe and operationalize the components of the work environment. Second, it can explain the interactions between the multiple components of the work system and the care processes. Third, it can demonstrate how the interactions between the work system and the care processes impact care outcomes. The model makes explicit the relationship between the work environment and the decision-making process. It distinguishes five components of the work system: person, tasks, tools and technology, environment, and organization.

Specifically, tools and technology refer to the elements that persons use to perform their tasks, such as a computerized care file, an electronic blood pressure monitor, and a telephone. ED studies have shown that technological breakdowns (computer downtime, blood pressure monitor out of order) can cause task interruptions [32, 49]. As this component is commonly explored when new technologies are introduced in the field of care, it will not be studied here, given that the nurses that will participate in the study are proficient in the use of the tools and technologies associated with the triage station.

The person component represents the core variable of the work system and refers not only to all the members of a team, which can include physicians, nurses, and other care providers, but also to the patients themselves and their families. In our study, the focus will be on nurses performing the task of emergency triage. For this component, Carayon et al. [45] recommended examining various elements, including personal, physical, and psychological characteristics, such as knowledge, motivation, and needs [45]. Triage studies have shown, in particular, that nurse education level, triage training, and work experience can influence triage accuracy, as can their aptitude to work fast and their confidence in their decision-making [28, 30, 35, 50].

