### Research questions

The questions asked in connection with the evaluation of preliminary effects are the following:
What is the acceptability level of our study design and the SG?What is the feasibility level of our study design and the SG?

The questions asked in connection with the evaluation of preliminary effects are the following:

Primary question:
What are the individual and combined effects of distractors on ED nurse triage accuracy?

Secondary questions:
2.How are nurse sociodemographic variables and personal characteristics related to triage accuracy?3.What is the relationship between nurse-perceived confidence and triage accuracy?

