### Proposed hypotheses

We propose the following hypotheses informed by the SEIPS theoretical model [45]: (1) our protocol is easy to implement in a real-life situation and emergency nurses can easily participate and are happy to adhere to our study, (2) exposure to a distractor will lower nurse triage accuracy and inter-rater reliability, (3) exposure to two distractors will lower nurse triage accuracy and inter-rater reliability more so than exposure to only one distractor, (4) nurse work experience is positively related to triage accuracy, and (5) nurse-perceived confidence is positively related to triage accuracy.

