## Method

### Study design

In order to evidence the effects of noise and task interruptions on nurse triage accuracy, we will carry out a 2 × 2 factorial randomized controlled trial [65]. A factorial design will be used given that two independent variables will be considered (noise and task interruptions) and that we will evaluate not only the effect of each variable on the dependent variable (nurse triage accuracy), but also their combined effect [65, 66]. The design will follow the CONSORT guidelines [67] and drive the structure of the trial and the choice of control, an analysis of study benefits, the quality and reliability of the intervention, a description of the population, the randomization procedure, and the statistical analysis plan.

This factorial design will allow us to create four groups: one control group and three experimental groups (A, B, C). While triaging the clinical vignettes, nurses in the control group will not be exposed to distractors. Nurses in experimental groups will be exposed to noise (group A), task interruptions (group B), or both noise and task interruptions (group C). Nurses will be block-randomized across the four groups by a computer program. The groups will be of equal size or as similar as possible in this regard.

The study design comprises repeated measures. We will collect sociodemographic and personal data from participants before they begin evaluating the clinical vignettes. Then, during the evaluation of each clinical vignette, the following data will be gathered systematically: (1) emergency level assigned, (2) level of perceived confidence in emergency level assignment, and (3) duration of each clinical vignette evaluation. Upon completing the evaluation of the 20 clinical vignettes, the participants will be asked to complete a questionnaire on the acceptability of the SG.

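### No allowance for clustering by nurse is stated for the experience and confidence analyses, although scores (expected N = 1,600) are their units and experience varies only between 80 nurses

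*Protocol article*

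**What the plan says.** The Data analysis plan sorts analyses by unit. Nurses (expected N = 80) are the units for the descriptive analyses. For the rest it says that "the assigned triage scale scores will be the analysis units for the correlational analyses", the count being given as "number of nurses multiplied by number of vignettes", 80 × 20 = 1,600. Four steps follow. Only the fourth, which compares the groups to estimate the distractor effects, names a model: a multinomial regression with a random intercept. One significance level, p ≤ 0.05, applies to all analyses.

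The other inferential aims concern nurse characteristics and confidence. Hypothesis 4 is that "nurse work experience is positively related to triage accuracy"; hypothesis 5 says the same of perceived confidence. One secondary question asks "How are nurse sociodemographic variables and personal characteristics related to triage accuracy". None of the four steps names a model for these.

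On timing, Study design says: "We will collect sociodemographic and personal data from participants before they begin evaluating the clinical vignettes". The Instruments section lists "total number of years of experience, number of years in current department" among the questionnaire items. Confidence is rated after every vignette. The Theoretical framework reports earlier evidence that "nurse education level, triage training, and work experience can influence triage accuracy".

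**The concern.** A variable measured once per nurse takes at most 80 distinct values, however many vignettes each nurse completes. Repeating it over 20 rows and testing it as though the rows were independent gives a standard error that is too small. The plan fixes the score as the unit for these analyses and attaches the within-nurse term to a different one, so an analyst who follows the text literally could run exactly that test.

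The stake is a false signal for hypothesis 4. The Discussion says the results will inform a larger study that is also meant to identify sociodemographic factors in accuracy, so a spurious experience effect could carry over into its design.

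Confidence raises a milder question. It is rated after exposure to the assigned condition, so a correlation pooled over four groups could mix differences between groups and between nurses with the relationship that hypothesis 5 is about.

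**Working it through.** **Inputs from the protocol.** Population and sampling: accuracy 0.85 in controls, a decline of 0.10, ICC between vignettes of the same nurse no more than 0.03, 20 nurses per group, power at least 0.80. Data analysis plan: 20 vignettes per nurse, 80 nurses, 1,600 scores, level 0.05. Sidedness is not stated; two-sided is assumed.

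**Step 1: reproduce the plan's own figure.**
- Two proportions, 0.85 against 0.75, two-sided 5%, power 0.80: n = [1.96·√(2 × 0.80 × 0.20) + 0.8416·√(0.85 × 0.15 + 0.75 × 0.25)]² / 0.10² = (1.1087 + 0.4723)² / 0.01 ≈ 250 independent scores per group.
- Design effect: 1 + (20 − 1) × 0.03 = 1.57.
- Nurses per group: 250 × 1.57 / 20 = 19.6, so 20. Without the design effect it would be 250 / 20 = 12.5.
- Power with 400 / 1.57 = 254.8 effective scores per group: 0.807. A beta-binomial simulation with a nurse-level t-test (8,000 runs) gives 0.790.

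The stated 20 per group is therefore reproduced, and only when clustering within nurse is counted.

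**Step 2: a predictor that is constant within nurse, tested as if scores were independent.** The full design effect applies. Actual type I error = 2·[1 − Φ(1.96 / √DEFF)].

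| ICC | Status | DEFF | 1.96 / √DEFF | Type I error |
|---|---|---|---|---|
| 0.03 | protocol's ceiling | 1.57 | 1.564 | 0.118 |
| 0.05 | assumed | 1.95 | 1.404 | 0.160 |
| 0.10 | assumed | 2.90 | 1.151 | 0.250 |

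Simulating 80 nurses × 20 scores with no experience effect (8,000 runs) gives 0.125 at ICC 0.03 and 0.251 at 0.10 for the naive test. A nurse-level correlation (n = 80) holds at 0.047 in both cases.

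The correct standard error is √1.57 = 1.25 times the naive one at ICC 0.03. Equivalently, the 1,600 scores carry the information of 1,600 / 1.57 ≈ 1,019 independent scores for this predictor.

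**Step 3: confidence.** It varies from vignette to vignette, so the score is a proper row for it. The factor 1 + 19 × ICC assumes a predictor with no within-nurse variation, and so does not apply in full. The protocol gives no figure for how much of the variation in confidence lies between nurses, so no inflation is computed.

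**Step 4: what adjusting the group comparison for experience would bring.** On the proportion scale, the variance of a group mean is proportional to (1 − ICC) + 20 × ICC = 0.97 + 0.60 = 1.57. If experience explains a share R² of the between-nurse part, the ratio becomes [0.97 + 0.60 × (1 − R²)] / 1.57.
- R² = 0.10: 1.51 / 1.57 = 0.96, a cut of about 4%.
- R² = 0.30: 1.39 / 1.57 = 0.89, a cut of about 11%.

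Both R² values are assumptions. The calculation is a linear approximation to the multinomial model.

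**The case against.** The strongest reply is that naming scores as units does not mean treating them as independent. The plan divides analyses into descriptive and correlational. The random-intercept regression is not descriptive, so on that division it belongs with the correlational analyses, and the 1,600 scores may simply be its level-1 rows. The remedy proposed here uses the same rows. The protocol also calls the design one of repeated measures and counts within-nurse correlation in its sample size. All of this stands. A reader might infer that clustering is ignored for hypotheses 4 and 5, but the text says no such thing; it leaves the matter unstated. The reply does not remove the gap, because the random intercept is tied in words to the distractor comparison alone.

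A reader might also infer that leaving experience out of the group comparison is an error. The documents do not support that. The fourth step lists no covariates and excludes none, and a covariate list is commonly left to a fuller plan. An unadjusted comparison of randomised groups is valid, its standard error already allows for chance imbalance, and the stated power reproduces without adjustment.

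Two further limits stand. ICCs above 0.03 exceed the protocol's own ceiling. And no passage says that distractors change confidence: the hypotheses concern accuracy and inter-rater reliability, so an effect on confidence is a possibility only. Because group is randomised and experience is recorded beforehand, group does not systematically confound hypothesis 4.

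Finally, this is a pilot and hypotheses 4 and 5 are secondary, which limits the consequences.

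**Conclusion.** The point holds as an unstated allowance for clustering, not as a demonstrated error. If the score-level unit were applied literally to experience, with scores treated as independent, a nominal 5% test would reject about 12% of the time under the null at the protocol's ICC ceiling of 0.03, more than twice the nominal rate. At a lower ICC the inflation is smaller. The figures of 0.16 and 0.25 hold only under the assumed ICCs of 0.05 and 0.10. All rest on a two-sided test and 20 completed vignettes per nurse. For confidence the concern is qualitative.

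The primary comparison is sound as described. Adding experience to it is a free improvement, worth about 4–11% of contrast variance if experience explains 10–30% of between-nurse variance, a share that the protocol does not give.

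**What to change.** Add one sentence to the Data analysis plan: the analyses of experience and of confidence against accuracy use the nurse random-intercept model with group included. For experience, a nurse-level analysis with n = 80 is an acceptable alternative.

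As an optional gain, prespecify years of experience as a covariate in the random-intercept multinomial group comparison, and say which of the two recorded experience measures is meant. Do not adjust that comparison for confidence or vignette duration: both are measured after exposure to the distractors. The Theoretical framework says that duration will be considered in the analyses, so the plan should make clear that this is not as a covariate there.

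The cost is wording only. The data are already to be collected, and no extra nurses are needed. The standard error for the experience analysis becomes wider than under independence, by a factor of about 1.25 at ICC 0.03.

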### Population and sampling

This multi-site study will be carried out in EDs where the SETS® is used. This is the case in 20 private and public care facilities in the five cantons of the French-speaking part of Switzerland (Geneva, Vaud, Fribourg, Jura, Neuchâtel). The population will consist of nurses who perform triage in these facilities. This corresponds to an accessible population of 454 nurses. The eligibility criteria will be similar to those used in previous studies of triage accuracy [27, 35, 68]. Specifically, to participate in our study, nurses must (1) consent to participate and (2) perform triage in one of the EDs where the SETS® is used. Nurses will be block-randomized across the four groups. We established a size of 20 nurses per group, for a total of 80. Around 18% of the accessible population is included, a non-negligible percentage that leaves, nonetheless, an ample margin for the recruitment for the future randomized control trial.

This sample size allows the inclusion of, at least, few nurses from each hospital providing an overview of all the emergency units of the hospitals in French-speaking Switzerland. Therefore, we can assume that our sample provides a sufficient heterogeneity to test acceptability and feasibility of our protocol. Moreover, assuming an accurate triage rate of 0.85 for the control group, a decline of 0.1 in the experimental groups, and an intraclass correlation (that is, between vignettes triaged by a same nurse) of no more than 0.03, we estimated through simulations that each group would need to comprise at least 20 participants to obtain a power of at least 0.80 in order to answer the primary research question. Consequently, we will aim to form a convenience sample of at least 80 nurses, and we will cease recruitment once this target is reached.

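### The stated power of at least 0.80 rests on binary accuracy, but the planned three-level multinomial model names no deciding test, and its joint and per-logit tests do not secure that power

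*Protocol article*

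**What the plan says.** Under Population and sampling the article gives its assumptions for power: "assuming an accurate triage rate of 0.85 for the control group, a decline of 0.1 in the experimental groups", with "an intraclass correlation (that is, between vignettes triaged by a same nurse) of no more than 0.03". The requirement it derives by simulation reads: "each group would need to comprise at least 20 participants to obtain a power of at least 0.80 in order to answer the primary research". The size is fixed accordingly: "We established a size of 20 nurses per group, for a total of 80". No rate of overtriage or undertriage is assumed, and the model that was simulated is not named.

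The primary question, under Research questions, asks for the individual and combined effects of distractors on triage accuracy. The second and third hypotheses are framed in the same way: distractors lower accuracy.

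The Data analysis plan then sets the outcome: "The results of the comparison will be a three-level multinomial variable: accurate triage (nurse score same as gold standard"), overtriage and undertriage. The groups are to be compared "using a random-intercept multinomial regression model", at a significance level of 0.05 for all analyses. Which parameter or test of that model answers the accuracy question is not stated.

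**The concern.** The question and the sample size concern one number per group, the probability of accurate triage. The model splits the errors in two, so each comparison of a group with control has two log-odds ratios: overtriage against accurate, and undertriage against accurate. The tests that a multinomial fit usually reports are those two single-logit tests, or their joint test on 2 degrees of freedom. Their power depends on how the errors divide between over- and undertriage, and the sample size statement assumes nothing about that.

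Two things are at stake. The promised power may not apply to the analysis that is run. The two logits may also disagree, one significant and the other not, on a question with a single answer. The results are meant to inform a large follow-up study, so an ambiguous primary result would carry forward.

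**Working it through.** **Inputs from the article.** Accurate rate 0.85 in control and 0.85 − 0.10 = 0.75 in an experimental group; intraclass correlation 0.03 (the stated upper bound); 20 nurses per group; 20 vignettes per nurse; significance level 0.05.

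**Assumptions added here.** Two-sided test; one group against control; no multiplicity adjustment; the same design effect for every outcome category; the error splits shown below.

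**Effective sample size.** Design effect = 1 + (20 − 1) × 0.03 = 1.57. Scores per group = 20 × 20 = 400. Effective n = 400 / 1.57 = 254.8.

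**Step 1: reproduce the stated figure as a binary comparison.**
- Log-odds difference = ln(0.75/0.25) − ln(0.85/0.15) = −0.636.
- SE = √[(1/0.75 + 1/0.25 + 1/0.85 + 1/0.15) / 254.8] = 0.227.
- |z| = 2.80; power = Φ(2.80 − 1.96) = 0.80.
- The usual two-proportion formula gives power 0.807. It needs 250 independent scores per group, and 250 × 1.57 / 20 = 19.6, so 20 nurses.

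Both the power and the group size match the article.

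**Step 2: the multinomial tests on the same effective n.** Write p₀ for accurate and pⱼ for an error type, C for control and E for experimental.
- Log-odds ratio: βⱼ = ln(pⱼE/p₀E) − ln(pⱼC/p₀C).
- Variance: (1/pⱼE + 1/p₀E + 1/pⱼC + 1/p₀C) / 254.8.
- Covariance of the two logits: (1/p₀E + 1/p₀C) / 254.8 = (1/0.75 + 1/0.85) / 254.8 = 0.00985.
- Joint Wald noncentrality: β′V⁻¹β, referred to a noncentral chi-square with 2 df.

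Worked case, even split (0.85/0.075/0.075 against 0.75/0.125/0.125): each β = 0.636, SE = √[(1/0.125 + 1/0.75 + 1/0.075 + 1/0.85) / 254.8] = 0.306, z = 2.08, power 0.55. Joint noncentrality = 7.82, power 0.71.

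| Control over/under | Experimental over/under | z, over / under | Single-logit power, over / under | Joint noncentrality | Joint 2-df power |
|---|---|---|---|---|---|
| 0.075 / 0.075 | 0.125 / 0.125 | 2.08 / 2.08 | 0.55 / 0.55 | 7.82 | 0.71 |
| 0.03 / 0.12 | 0.05 / 0.20 | 1.36 / 2.55 | 0.27 / 0.72 | 7.82 | 0.71 |
| 0.075 / 0.075 | 0.095 / 0.155 (80% of the decline in undertriage) | 1.12 / 2.88 | 0.20 / 0.82 | 8.97 | 0.77 |
| 0.075 / 0.075 | 0.075 / 0.175 (all of the decline in undertriage) | 0.37 / 3.34 | 0.07 / 0.92 | 11.18 | 0.86 |

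When both error types rise in the same proportion, joint power is 0.71 whatever the split (rows 1 and 2). That is the lowest joint value found.

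**Step 3: sensitivity to method.** For the even split, Pearson and likelihood-ratio versions of the joint test give 0.715 and 0.719. A Dirichlet-multinomial simulation gives 0.75 for the joint test and 0.57 to 0.58 per logit. With the whole decline in undertriage, the Pearson, likelihood-ratio and simulated joint power is 0.88 to 0.89.

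**Step 4: sample size at an even split.** Power of 0.80 needs about 25 nurses per group for the joint test (Wald 0.806 at 25, 0.789 at 24), or about 37 per group for each logit (0.807 at 37, 0.797 at 36).

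**The case against.** **The shortfall is conditional.** A reader might infer that power falls to 0.71, or to 0.55 per contrast. The article does not support that as a plain statement, because it gives no over- or undertriage rates. The 0.71 needs a proportional rise, the 0.55 an even split, and joint power exceeds 0.80 if the decline is concentrated in one error type. This stands, and the figures must be read as conditional.

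**The model can still test accuracy.** A reader might also infer that a multinomial model offers no single test of accuracy. It does: the probability of accurate triage can be contrasted between groups from the same fit, with power close to the binary 0.80 (approximately so with a random intercept). This also stands. The loss comes from using the joint or single-logit tests, which the plan neither chooses nor excludes.

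**The simulation may have been multinomial.** The simulated model is not named, so this cannot be strictly excluded. But the stated inputs do not define a multinomial model, and the binary calculation gives exactly 20 nurses.

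**The detail belongs in a fuller plan.** Leaving the deciding contrast to an analysis plan would be no finding by itself. Here the article itself fixes the outcome, the model and the power claim, and they do not fit together.

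**The contrast matters too.** In the factorial design a main effect pools 40 against 40 nurses. If effects are additive (0.85/0.75/0.75/0.65, assumed, even split), power is about 0.92 for the joint test and 0.79 per logit. If all experimental groups sit at 0.75, as the wording "a decline of 0.1 in the experimental groups" can be read, the main effect is only 0.80 against 0.75, where even binary power is 0.48. Pooling does not reliably remove the problem.

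**This is a pilot, and direction of error matters clinically.** Both are fair. They support keeping the three-level outcome, and they do not tell the reader which test carries the stated power.

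**Impossible errors.** The vignettes are such that "all four emergency levels of the SETS will be covered", so the most urgent cannot be overtriaged and the least urgent cannot be undertriaged. A reader might take this as further evidence against the power. It is not: all groups receive the same series, so the dilution is alike in every group, causes no between-group bias and leaves accuracy untouched.

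**Conclusion.** The concern holds as a mismatch. The stated power of at least 0.80 is the power of a binary comparison of 0.85 with 0.75, while the analysis named for the same question is three-level, with no deciding test. Under that model's joint test, power for one group against control is about 0.71 to 0.86 (Wald) over the splits examined. Per logit it is about 0.55 at an even split and between about 0.07 and 0.92 otherwise. Whether 0.80 is reached therefore depends on a division of errors that the article does not state.

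These figures rest on the article's own rates and intraclass correlation, a two-sided 0.05 level without multiplicity adjustment, all 20 vignettes completed, and assumed error splits. They do not show that the trial is underpowered for accuracy: a test on accurate against not accurate keeps the stated power.

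**What to change.** **Preferred.** State in the Data analysis plan that the primary question is decided by a random-intercept logistic regression of accurate (yes/no) or, to the same end, by a prespecified contrast on the probability of accurate triage from the multinomial fit. Keep the multinomial model of over- and undertriage as a secondary analysis that describes the direction of error. This matches the inputs under Population and sampling and needs no extra nurses. The cost is wording, plus one real downside: direction of error becomes a secondary result.

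**Alternative.** Keep the multinomial model as primary, state the assumed over- and undertriage rates in each group, name the deciding test (joint or per logit), and rerun and restate the power. At an even split, 0.80 would need about 25 nurses per group for the joint test (25 × 4 = 100 in all) or about 37 for each logit (37 × 4 = 148), against the planned 80.

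Under either option, name the model that was simulated beside the power statement.
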